### Secondary analysis

***1. Investigate accuracy and reliability of mobile eye-tracking during gait in people with PD and older adults***

To analyse reliability; repeated-measure
*t*-tests, Bland and Altman plots, intra-class correlation coefficients (Model 2, 1) and Pearson’s correlations (or non-parametric equivalents) will be used to assess bias, absolute and relative agreement and consistency of saccadic outcomes measured with the Dikablis eye-tracker on two separate occasions a week apart. A similar statistical approach will be used to assess accuracy of the Dikablis system against targets of a known angle (5°, 10° and 15°).

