^16^. Saccades are impaired in PD and exhibit reduced speed, amplitudes and latencies
^17–
22^. Impaired saccadic eye movements, with reduced latencies and increased error rates have also been reported in PD dementia and dementia with Lewy Bodies, further implicating central neuro-degeneration as a determinant of ocular motor function
^23,
24^. However, the specific contribution of cognitive and/or visual functions to visual sampling during gait in PD and how this impacts gait deficit is currently poorly understood.

Much of the previous saccadic activity research is limited due to the almost exclusive use of static testing protocols (e.g. computerised tasks in sitting)
^18,
25^, which may not be applicable to real-world situations. A recent review of dynamic motor tasks (e.g. gait, obstacle crossing, turning etc.) in PD and older adults
^15^, demonstrated that visual sampling is task dependent and relates to specific goals
^26^. For example: during locomotion over even terrain, saccades may not be required. Over uneven (complex) terrain or during turning saccadic frequency, amplitude and fixations increase
^27–
30^. However many previous visual sampling protocols during dynamic task studies use small cohorts and often do not assess cognitive or visual functions
^15^, which limits interpretation and conclusions regarding underlying mechanisms. Visual sampling during gait therefore has not been fully investigated and further research is required to understand this important feature of gait control. Improved understanding will assist with interventions to improve gait performance in PD.

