### Equipment

Visual sampling (the combination of saccades and fixations) was assessed with a Dikablis (Ergoneers, Germany) head-mounted infra-red eye tracking system, synchronised with a 3D motion capture system (Vicon, Oxford, UK) and an electrooculography (EOG) system (Zerowire, Aurion, Italy), to allow for simultaneous and comprehensive recording and analysis of gait and eye movement data. Dikablis calibration was performed while standing using the manufacturer 4-point procedure for each participant prior to data collection. Similar to our previous research
^29^, EOG was also calibrated prior to data collection via asking participants to blink for 30 secs and move their eyes horizontally between set-distance visual targets (5°, 10° and 15°) for 30 secs in time with an auditory cue (a metronome beat) while seated.

The Dikablis eye-tracker recorded eye movement using an infra-red camera
^63–
65^, this data was combined with EOG data which involves two small electrodes being applied bi-temporally on the forehead of the participant. Importantly, the Dikablis has an adequate sampling frequency (50Hz) to detect saccades during gait
^66,
67^ and EOG has a high sampling frequency (1000Hz) which allows accurate acquisition of specific visual sampling characteristics such as velocity, acceleration, distance etc.
^15^. The Dikablis device includes two aspects; a head unit and a transmitter bag. Both the head unit (approx. the same size as a pair of glasses) and the bag (approx. 1kg) are lightweight. The head unit was taped, with a small amount of double sided tape, to the forehead of the participants to prevent error due to slippage. Eye movement data from the Dikablis was collected at 50Hz and from the EOG system at 1000Hz; this was saved onto a computer to be analysed using proprietary software
^66^.

Video recording and the Vicon 3D motion capture system recorded participants movement during walking using a camcorder and infra-red sensors attached to the skin of the participants at specific locations (

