### Accuracy and reliability testing of visual sampling

Mobile infra-red eye-tracking and EOG have been shown to be a valid and reliable method for assessing saccadic activity in younger adults
^69^, and both have previously been used in older adults and in people with PD
^29,
70–
73^. We were interested in the accuracy and test-retest reliability of mobile eye-tracking in people with PD and older adult controls to ensure the robustness of data interpretation. Therefore, a subgroup (PD and control; up to n=25) were asked to return approx. one week later for a second and third visit for accuracy and test re-test reliability testing (
Table 2). The Dikablis eye-tracker recorded eye movement and was used in the same manner as the previous study
^63–
65^, combined with video recording of individuals body movement and a tri-axial accelerometer (Axivitiy, AX3, York, UK) recording head movement.

**Table 2. T2:** Study protocol overview.

Participants (n = 100)	Session 1 (up to 150min)	Session 2 (up to 60min)	Session 3 (up to 60min)
1. Older adult controls (n = 40) 2. Parkinson’s disease (n = 60)	Applicable to all participants (n=100) • Initial screening, cognitive and visual function assessments (45–60min) • Informed consent • Demographic and diagnostic evaluation **Global cognitive assessments:** • MoCA • ACE-R **Specific cognitive domain** **assessment:** • JLO • CLOX 1 and 2 • VOSP battery • Attention CDR battery **Visual function assessments:** • Visual acuity • Contrast sensitivity **PD-Specific assessments:** • UPDRS • Hoehn and Yahr • FOG-questionnaire **Common assessments:** • GDS-15 • FES-I Visual sampling during gait testing in gait laboratory (60–90min)	Applicable; for a subgroup of PD and control participants (n=25) Approx. 1 week after session 1 1 ^st^ Reliability testing (45–60min) • Repeat visual sampling during gait testing in gait laboratory (single task, without a visual cue) • Sit, stand and walk on a treadmill while making eye- movements to set distance targets (5°, 10° and 15°)	Applicable; for a subgroup of PD and control participants (n=25) Approx. 1 week after session 2 2 ^nd^ Reliability testing (45–60min) • Sit, stand and walk on a treadmill while making eye- movements to set distance targets (5°, 10° and 15°)

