In the second session the sub-group of participants were asked to repeat the walking tasks from session 1 (single task, without a visual cue) to provide visual sampling during gait reliability data. Accuracy of visual sampling measurement was determined by asking participants to sit (with chin rest
*in situ*), stand (without moving their head) and walk (free head movement) on a treadmill, while performing several eye movements to visual targets (horizontal and vertical visual angles such as 5°, 10°, 15°) in time with an auditory cue (a metronome). The subgroup was asked to return for a third visit (within approx. 1 week of the second visit) to repeat the accuracy testing (as above) in order to derive test-retest reliability results.

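### Dikablis accuracy is judged against the target angle alone, so in people with PD the eye's own undershoot may be counted as tracker error

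*Protocol article*

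**What the plan says.** The Secondary analysis section lists paired t-tests, Bland-Altman plots, intra-class correlations and Pearson correlations for saccadic outcomes measured on two occasions. It then carries the method over to accuracy: "A similar statistical approach will be used to assess accuracy of the Dikablis system against targets of a known angle". The angles are 5°, 10° and 15°.

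The section on accuracy and reliability testing says where the data come from. A subgroup of up to 25, with both PD and control participants, is seen seated with a chin rest, standing with the head still, and walking, "performing several eye movements to visual targets (horizontal and vertical visual angles such as 5°, 10°, 15°) in time with an auditory cue". In the last condition they "walk (free head movement) on a treadmill". Besides the Dikablis, that section names only video of body movement and an accelerometer "recording head movement".

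The Introduction states: "Saccades are impaired in PD and exhibit reduced speed, amplitudes and latencies".

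Under Equipment, EOG is calibrated for each participant on the same angles, seated: participants "move their eyes horizontally between set-distance visual targets (5°, 10° and 15°) for 30 secs in time with an auditory cue". How the voltage is converted to degrees is not stated.

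**The concern.** A target at 10° shows where the eye was asked to go, not where it went. Using it as the reference for a device assumes that the participant's eye covered the whole angle. The protocol's own premise is that in PD it tends not to, and people with PD are one of the two groups in the accuracy subgroup.

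If saccade amplitude is set against the target, a participant's shortfall and a tracker's error fall into the same difference, and none of the listed statistics can separate them. The result could describe the Dikablis as biased, and more so in PD, when part or all of the gap belongs to the eye. This bears on a declared aim. The Introduction faults earlier work for not reporting device accuracy, and the Discussion expects to supply the first such evidence during gait in these groups.

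**Working it through.** **No figure to reproduce.** The article states no accuracy limit, no expected bias and no size for the PD amplitude reduction. All gains below are assumptions.

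**Inputs.** Target angles T = 5°, 10°, 15° (Secondary analysis; accuracy and reliability testing). Direction of the PD effect: reduced amplitude (Introduction). Eye gain g = first-saccade amplitude / target angle, assumed 0.95 to 0.80.

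**Step 1: what the comparison measures.** Let the eye turn by gT and the tracker report that turn with error e. Then

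measured - target = (gT + e) - T = e + T(g - 1).

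The first term is device error. The second is the participant's shortfall.

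**Step 2: apparent bias with a perfect tracker (e = 0).**

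| Assumed gain g | T = 5° | T = 10° | T = 15° |
|---|---|---|---|
| 0.95 | -0.25° | -0.5° | -0.75° |
| 0.90 | -0.5° | -1.0° | -1.5° |
| 0.85 | -0.75° | -1.5° | -2.25° |
| 0.80 | -1.0° | -2.0° | -3.0° |

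For example, 10 × (0.90 - 1) = -1.0.

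**Step 3: can the data tell the two terms apart?** Suppose instead that the eye is perfect and the tracker under-reads by 10%. The errors are -0.5°, -1.0° and -1.5°, identical to the 0.90 row. A Bland-Altman plot shows the same slope either way. Pooling the groups does not help: with a share p of the subgroup having PD and a control gain of 1, the pooled bias at 10° for g = 0.90 is p × (-1.0°). It then depends on the PD-control mix, which the article does not give.

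**Step 4: is there another measure of the eye?** Body video and a head accelerometer do not record eye rotation. EOG is not named for the accuracy task.

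**Step 5: the three conditions differ.** With the chin rest, or standing with the head still, the head is not meant to contribute, so T(g - 1) is the main contaminant. If the eye then corrects and settles on the target, the settled position has g close to 1 and the term drops out. On the treadmill the head is free. Part of the target angle can be covered by the head, so even a settled eye-in-head angle need not equal T.

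**Step 6: EOG, conditional.** If the EOG scale were set so that the paced first saccade equals T, a person with calibration gain g would have amplitude, velocity and acceleration multiplied by 1/g: 1.05, 1.11, 1.18 or 1.25 for the four gains above. If the scale came from settled positions, the factor would be 1.

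**The case against.** The strongest reply is that the article does not say which quantity is extracted. It names the target as the reference but not whether first-saccade amplitude or gaze position on the target is compared, and signal-processing detail may sit in a fuller document. This stands in part, and is why the point is worded with an if. But the reference itself is stated, the approach is borrowed from one for saccadic outcomes, and settled position is not mentioned, so saccade amplitude is the natural reading.

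It is also fair that no gold-standard device exists, as the Introduction says, so known angles are an understandable choice. Control results and the seated, standing and walking comparison do say something about the device. They do not isolate it in PD.

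The Introduction gives neither a size nor a task for the reduced amplitudes, so nothing shows that it applies in full to visible targets paced by a metronome. That stands, and it limits the table to illustration.

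A reader might go further and infer that EOG calibration removes the PD deficit from the PD-control contrasts. The documents do not support that. The Equipment section does not say how EOG is scaled. Even with scaling on the first saccade, the reported PD/control ratio would be gait gain / calibration gain (control gain taken as 1 in both), which equals 1 only if seated paced saccades and saccades during walking fall short by the same proportion. With 0.80 in gait and 0.95 in calibration it is 0.80 / 0.95 = 0.84, so most of the deficit remains. The Dikablis has its own four-point calibration, so the scaling question concerns EOG alone.

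**Conclusion.** The point holds for the accuracy analysis. The target angle is the only reference, no independent measure of eye rotation is described, and the protocol itself expects reduced saccade amplitude in PD. If saccade amplitude is compared with the target, the accuracy figure mixes device error with participant undershoot, and in the direction that makes the device look worse in PD. At an assumed gain of 0.90 and with a perfect tracker, the false bias is -1.0° at 10° and -1.5° at 15°. Over gains of 0.95 to 0.80 it runs from -0.5° to -2.0° at 10°. It disappears for the head-still conditions if settled eye position is already what is used and the eye does settle on the target.

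The EOG point is a precaution only. A reader might also infer damage to the primary outcome, but saccade frequency is a count per second, not an angle, and the article does not say that its detection depends on the calibrated scale. Test-retest reliability is largely untouched, since a stable undershoot repeats from visit to visit.

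**What to change.** In the Secondary analysis section:

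- **Seated and standing conditions.** Compute Dikablis accuracy from the settled eye position on the target, after corrective saccades. Define settled by a rule fitted to the actual beat interval, which the article does not give. Report bias and limits of agreement separately for PD and controls.
- **Saccadic gain.** Report first-saccade amplitude divided by target angle as a participant outcome, not as device error.
- **Treadmill condition.** Describe measured minus target as a combined eye, head and device discrepancy, and do not call it device accuracy.
- **EOG, as a precaution.** State that each person's scale is taken from settled positions at each target. If that is already the practice, one sentence closes the matter.

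The cost is small. Data collection ended in July 2015 and the analysis is still described in the future tense, so this is wording plus re-extraction from recordings already made. There are two downsides. Beats on which the eye does not settle give no accuracy value, and their number should be reported by group. Accuracy of settled position also does not by itself validate saccade amplitude during movement, and the report should say so.

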### Analysis common to all studies

Statistical analysis will be undertaken using SPSS version 21 (SPPS, Inc. an IBM company). Demographic characteristics and baseline data will be summarized using descriptive statistics, including means, standard deviations, median, minimum, maximum and inter-quartile ranges for continuous or ordinal data and percentages for categorical data. The descriptive statistics will be tabulated and presented graphically for clarity. One-sample Kolmogorov-Smirnov tests will be used to check for normally distributed data. Non-normally distributed continuous distributions will be transformed where appropriate to meet the requirements of parametric tests; otherwise equivalent non-parametric tests will be adopted. Data will also be assessed graphically (such as histograms or scatter plots) for clarity of information. As this is an exploratory study a threshold of
*p* < .05 (two-sided) will guide statistical interpretation. A brief summary of participant demographic and clinical outcomes is provided in
Table 3.

**Table 3. T3:** Brief summary of demographic and clinical features.

		Control (n=40) Mean (SD)	PD (n=60) Mean (SD)	***p***
Demographic	Age (years)	66.93 (10.86)	67.77 (7.60)	.649
	Sex	17M/23F	38M/22F	**.041** †
	Education (years)	14.80 (3.03)	13.28 (3.61)	**.031 ***
	Depression scale (GDS-15)	0.70 (0.88)	2.80 (2.77)	**.000 ***
	Falls efficacy scale (FES-I)	18.98 (4.15)	25.48 (8.99)	**.000 ***
Clinical	Hoehn and Yahr stage (H&Y)	-	I (21)/II (33)/III (6)	-
	Disease duration (months)	-	75.38 (75.50)	-
	UPDRS part III	-	37.13 (13.84)	-
	FOGQ	-	4.33 (7.21)	-
	LED	-	629.49 (412.82)	-

*independent t-test significance level p<.05, † = X², LED = levodopa equivalent dose, FOGQ = freezing of gait questionnaire and UPDRS III = unified Parkinson’s disease rating scale (motor subsection)

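### Carrying ICC(2,1) and Pearson correlation over to accuracy against fixed targets adds two coefficients that are degenerate at each target and, if pooled, mostly reflect the target spread

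*Protocol article*

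**What the plan says.** Under Secondary analysis, item 1, the protocol article plans repeated-measure t-tests, Bland-Altman plots and two kinds of coefficient for test-retest reliability: "intra-class correlation coefficients (Model 2, 1) and Pearson’s correlations (or non-parametric equivalents) will be used to assess bias, absolute and relative agreement and consistency" of the saccadic outcomes on two occasions a week apart. The next sentence turns to accuracy: "A similar statistical approach will be used to assess accuracy of the Dikablis system against targets of a known angle", with the angles given as 5°, 10° and 15°. The article names no further accuracy method, does not exclude any of the four, and does not say whether the three angles are analysed separately or together.

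The section on accuracy and reliability testing describes the reference. Participants sit, stand and walk on a treadmill while moving their eyes to set targets ("horizontal and vertical visual angles such as 5°, 10°, 15°) in time with an auditory cue (a metronome"). The angles are set by the experimenter and are the same for everyone. The data come from a subset of participants: "a subgroup (PD and control; up to n=25) were asked to return approx. one week later for a second and third visit".

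**The concern.** Correlation and ICC compare variation between subjects with measurement error. That suits two sessions in the same people, where both columns vary. In the accuracy comparison one column is a constant chosen by the investigators. At one target there is no between-subject variation in the reference for a coefficient to work with. Across pooled targets, the variation is whatever spread of angles was designed in.

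Accuracy and reliability of the tracker is the only secondary aim listed. The Introduction faults earlier work for not reporting device accuracy, and the Discussion expects this study to supply the first such evidence during gait in these populations. The same device also contributes to the primary outcome, saccade frequency. Later users could take a pooled coefficient as a property of the device when it owes much to the choice of targets.

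**Working it through.** **Inputs.** From the protocol: targets T = 5°, 10°, 15°; up to 25 people; ICC Model 2,1. The protocol states no error SD, bias, coefficient or acceptance threshold, so there is no figure of its own to reproduce. Assumed: random error SD s from 0.5° to 4°, constant bias b of 0°, 2° or 3°, gain g (reading divided by true angle) of 1 or 0.5.

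**One target.** Let x be the reading and c the constant target.
- Pearson: r = cov(x, c) / (SD(x) × SD(c)) = 0/0, undefined. Rank correlation fails in the same way, so the non-parametric option does not help.
- ICC(2,1): row means are (x + c)/2 with variance var(x)/4, so the row mean square is 2 × var(x)/4 = var(x)/2. The differences x − c have variance var(x), so the error mean square is also var(x)/2. The numerator, row minus error mean square, is exactly 0.
- In simulation (25 people × 3 targets, 1,000 data sets per scenario), r computed at the 10° target was undefined every time, and ICC at each target was zero to rounding (largest absolute value 2 × 10⁻¹⁵) in every scenario.

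**Targets pooled.** V = var(T) = (25 + 0 + 25)/3 = 16.67, so SD(T) = 4.08°. For reading x = b + gT + error, with B the mean bias over targets:
- r = g × 4.08 / √(g² × 16.67 + s²)
- ICC(2,1) ≈ 2gV / ((1 + g²)V + s² + B²)

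For example, with s = 2°, g = 1 and b = 0: r = 4.08/√20.67 = 0.90, and ICC = 33.33/37.33 = 0.89.

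| s (no bias, g = 1) | 95% limits (±1.96s) | r: formula / simulated | ICC: formula / simulated |
|---|---|---|---|
| 1° | ±2.0° | 0.971 / 0.972 | 0.971 / 0.971 |
| 2° | ±3.9° | 0.898 / 0.900 | 0.893 / 0.894 |
| 3° | ±5.9° | 0.806 / 0.810 | 0.787 / 0.791 |
| 4° | ±7.8° | 0.714 / 0.717 | 0.676 / 0.679 |

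**Dependence on the chosen angles.** Hold the device error at s = 2° and change only the targets:
- 5° and 10°: SD(T) = 2.5, r = 2.5/√(6.25 + 4) = 0.78
- 5°, 10° and 15°: r = 0.90
- left and right coded as ±5°, ±10°, ±15°: var(T) = (25 + 100 + 225)/3 = 116.67, r = 10.80/√120.67 = 0.98

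**Systematic error.**
- Bias 3°, s = 2°: r stays at 0.90; ICC = 33.33/(37.33 + 9) = 0.72.
- Bias 2°, s = 1°: r stays at 0.97; ICC = 33.33/(34.33 + 4) = 0.87.
- Half gain, s = 0.5°: errors of −2.5°, −5° and −7.5° at the three targets, so B = −5°. r = 2.04/√(4.17 + 0.25) = 0.97; ICC = 16.67/(20.83 + 0.25 + 25) = 0.36.

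Pearson does not see bias or gain error. ICC(2,1) does.

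**What still works.** The paired difference x − c gives a signed mean error and limits of agreement that do not depend on the target spread. At one target the Bland-Altman plot collapses to the line difference = 2 × (mean − c), but the bias and limits read from it remain correct.

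**The case against.** The accuracy sentence promises a similar approach, not an identical one, and the article condenses a fuller protocol. No sentence assigns ICC or Pearson to accuracy, and how the targets are handled could properly be left to an analysis plan. This stands as far as it goes: the carry-over is the plain reading rather than an express commitment, and pooling is only a possibility. It does not remove the point, because the sentence imports a list of methods, excludes none of them and offers no alternative.

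A reader might infer that the plan has no valid way to measure accuracy. The documents do not support that. The imported list begins with t-tests and Bland-Altman plots, which give bias and limits of agreement against a known angle, and the paragraph names bias among the things to be assessed.

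A reader might also infer that the plan would pass a poor tracker as excellent. That would require pooling and a reader who ignored the bias and limits reported beside the coefficients. A constant 3° error would show in those results and would also lower the ICC. At a single target an undefined r would be visibly degenerate and an ICC of zero would certify nothing. The protocol sets no r or ICC threshold for accepting the device.

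**Conclusion.** The point holds in a limited form. On the plain reading, two of the four methods carried over to accuracy are uninformative at each target and potentially misleading if targets are pooled. The single-target result is exact algebra and needs no assumption. The pooled figures rest on assumed error sizes and on pooling, which the text leaves open. The problem is greatest for Pearson; ICC(2,1) shares the dependence on target spread but responds to systematic error.

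Severity is moderate. The issue concerns a secondary aim of an exploratory study in at most 25 people, and the planned ANOVA, regression and structural equation models do not use these coefficients. Using ICC(2,1) and Bland-Altman between sessions is appropriate and is not questioned here.

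**What to change.** Replace the accuracy sentence so that ICC(2,1) and Pearson correlation apply to session-to-session reliability only. For accuracy, report for each target angle and each condition (sit, stand, walk) the signed mean error with 95% CI, the mean absolute error and the 95% limits of agreement, and state that accuracy conclusions rest on these. A mixed model for error with a random participant effect is an option, not a requirement, given the small subgroup.

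The change costs only wording and uses data the protocol already collects. The accuracy figures will look less favourable than pooled correlations would.
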